## Abstract

**Introduction:**

Genetic studies have identified the *GBA1* gene as a significant genetic risk factor for Parkinson’s disease (PD), with 10–15% of PD patients carrying *GBA1* variants. *GBA1* variants affect the glucocerebrosidase (GCase) enzyme, often leading to reduced GCase activity and associated altered lysosomal function, implicated in PD pathogenesis. Ambroxol, a small molecule widely used for respiratory diseases, has emerged as a potential therapeutic agent for PD, acting by increasing GCase activity. A phase 2 trial demonstrated ambroxol’s safety and efficacy in penetrating cerebrospinal fluid (CSF) and engaging with its target in PD patients, including those with *GBA1* variants.

**Methods:**

We present the protocol of the ASPro-PD trial, a phase 3, multicentre, randomised, double-blind, placebo-controlled trial, aimed at evaluating whether high-dose ambroxol improves motor and non-motor function in PD patients. The trial will enrol 330 PD patients with confirmed *GBA1* status and the primary outcome will be the combined score of parts I, II, and III of the Movement Disorders Society–Unified Parkinson’s Disease Rating Scale (MDS-UPDRS). The secondary outcomes include safety, impact on PD symptoms, and quality of life. Mechanistic and exploratory outcomes include biomarkers related to GCase activity, blood, and CSF biomarkers.

**Conclusions:**

This trial is the largest to date to study the effect of ambroxol in PD, utilise a genetically stratified PD population and will provide robust estimates of the efficacy of ambroxol in slowing PD clinical progression.

**Supplementary Information:**

The online version contains supplementary material available at 10.1007/s00415-026-13683-7.

## Introduction

According to the World Health Organisation, in 2019, 8.5 million people were living with Parkinson’s disease (PD) worldwide, and PD may have the fastest growing prevalence amongst neurodegenerative disorders [1]. Current therapy improves motor symptoms, but there is no intervention to slow progression.

Multiple associations between genetic variants and PD have been identified [2]. Variants in the *GBA1* gene are numerically the most important genetic risk factor for PD, with approximately 10–15% of individuals with PD carrying a *GBA1* variant [3–6]. *GBA1* encodes for the lysosomal hydrolase glucocerebrosidase (GCase), and *GBA1* variants are the cause of the autosomal recessive lysosomal storage disorder Gaucher disease (GD) [7]. Over 400 *GBA1* mutations have been described, and they are classified as severe or mild according to whether they cause the neuronopathic or non-neuronopathic form of GD [7]. Additional *GBA1* variants confer an increased risk of PD, but do not lead to GD and are thus referred to as risk variants [8].

*GBA1* variants can lead to reduced GCase activity and misfolded GCase proteins, with a cascade of effects that involve the autophagy–lysosomal pathway, lipid homeostasis, mitochondrial function, and endoplasmic reticulum stress [9].

Furthermore, *GBA1*/GCase pathology might be relevant even in “idiopathic” PD (i.e. no identified genetic variant), because reduction of GCase activity has been reported in individuals with PD without *GBA1* variants [10]. Given the importance of the *GBA1*/GCase pathway in PD, this has become a focus of intense research to develop interventions to slow clinical progression [11].

Evidence suggests that the small molecule ambroxol might be able to rescue GCase activity in *GBA1*-associated PD, and possibly in idiopathic PD [12–18].

Ambroxol has been widely used for the past 50 years as a mucolytic and bronchodilator agent at doses between 30 and 120 mg, with a good safety and tolerability profile [19]. Importantly, at high dosages, ambroxol can act as an inhibitory chaperone for mutant GCase, increasing its transport to the lysosome, where the acidic pH (in contrast to the cytosol) causes ambroxol to dissociate from mutant GCase, allowing it to exert its residual enzymatic function [20]. Ambroxol may also increase normal GCase transfer to the lysosome by its chaperone function and result in increased activity [20]. Ambroxol is also reported to increase the nuclear translocation of transcription factor EB, a master regulator of lysosomal biogenesis [17], which could lead to even further enhanced lysosomal function.

A phase 2 unblinded clinical trial studying the use of a high dosage of ambroxol (1260 mg/day) in PD participants, with and without *GBA1* variants, showed good penetration and target engagement in the CSF [21]. This study also indicated that at elevated dosages, ambroxol was well-tolerated in the PD population over a 6-month period, and did not adversely affect the efficacy of co-administered dopaminergic therapy [21].

Several additional trials are already underway to investigate the use of ambroxol in PD, PD-Dementia, and Dementia with Lewy bodies (DLB), as summarised in Table 1.

**Table 1 Tab1:** Previous and current trials exploring the use of ambroxol for the treatment of PD and DLB

Study name	Participants	Intervention	Duration of treatment	Primary outcome	References	(Estimated) Study completion
AIM-PD	8 *GBA1*-positive PD and 9 *GBA1*-negative PD	Ambroxol 1260 mg/day	186 days	CSF biomarkers, safety and tolerability	NCT02941822	Completed
AMBITIOUS	65 GBA1-positive PD	Ambroxol 1200 mg/day vs placebo	52 weeks	MoCA	NCT05287503	15 Dec 2024
Ambroxol as a novel disease-modifying treatment for Parkinson's disease dementia	15 LBD	Ambroxol 1350 mg/day vs placebo	52 weeks	MMSE	NCT04405596	Jan 2025
High-dose ambroxol in GBA1-related Parkinson	40 *GBA1* positive PD	Ambroxol 1200 mg/day (open label)	12 months	Safety and tolerability	NCT06193421	20 Apr 2025
ANeED	172 DLB	Ambroxol 1260 mg/day vs placebo	18 months	MMSE	NCT04588285	01 Jul 2025
GREAT	80 PD	Ambroxol 1800 mg/day vs placebo	48 weeks	MDS-UPDRS3 motor scale	NCT05830396	Jul 2025
Ambroxol as a novel disease-modifying treatment for Parkinson’s disease dementia	75 mild to moderate PD with dementia	Ambroxol 1050 mg/day vs ambroxol 525 mg/day vs placebo	52 weeks	ADAS-Cog and CGIC	NCT02914366	Dec 2025
APM002	240 PD cases	Ambroxol 1200 mg vs doxycycline 100 mg/day vs ambroxol 1200 mg + doxycycline 100 mg/day vs placebo	48 weeks	MDS-UPDRS	ACTRN12623000843651	May 2026

*PD* Parkinson disease, *CSF* cerebrospinal fluid, *ADAS-Cog* Alzheimer’s disease Assessment Scale–cognitive subscale, *CGIC* Clinician’s Global Impression of Change, MoCA Montreal Cognitive Assessment, *DLB* dementia with Lewy bodies, *MMSE* Mini Mental State Examination

The primary objective of ASPro-PD (Ambroxol to Slow Progression in Parkinson Disease) is to assess whether 1260 mg/day of oral ambroxol over two years in PD is associated with an improvement in motor and non-motor function, compared to placebo. Secondary objectives include the safety and tolerability of ambroxol, and the impact on other PD features and quality of life. Mechanistic and exploratory objectives include assessment of the effect of ambroxol on biofluid biomarkers of PD and to stratify results by *GBA1* status.

## Methods

### Design and study setting

ASPro-PD is a phase 3 multi-centre UK-based, randomised, double-blind, parallel-group, placebo-controlled trial, with a 104-week blinded treatment period, followed by a 26-week open-label extension. The open-label extension, whilst maintaining the blind of the first 104 weeks, provides an opportunity both to incorporate a short 6-month period of assessment of ambroxol in the original placebo group, and enables a total period of drug exposure to satisfy registration. A panel of patients, international experts, and charity representatives informed trial design.

This clinical trial will take place at NHS hospital outpatient clinics across the UK that are experienced in managing people with PD and conducting PD clinical trials.

This trial is sponsored by University College London and run by the Comprehensive Clinical Trials Unit (UCL CCTU). The trial received research ethics committee (research ethics committee reference number 24/WA/0231) approval and is registered on www.clinicaltrials.gov (NCT05778617).

### Participants

A total of 330 participants with a diagnosis of PD and known *GBA1* status (heterozygous variant carriers or wild-type) will be recruited over a period of 2 years. Participants should be already established on a stable dose of dopaminergic treatment for at least three months prior to randomisation. They should not have disabling dyskinesia or dementia. A list of current inclusion and exclusion criteria can be found in Supplementary Table 1, and a list of prohibited medications in Supplementary Table 2. The principal action of ambroxol, preclinical data, and the results of the AiM-PD study all support the hypothesis that this drug has potential benefit for PD patients either with or without *GBA1* variants [12, 17, 18, 20, 21]. This trial aims to recruit *GBA1* positive and negative patients in equal numbers and is powered to enable a comparison in response for the groups together (primary endpoint), with a secondary outcome comparing treatment effect in the subgroups defined by *GBA1* status.

Participants meeting the inclusion and exclusion criteria will be recruited within 28 days of the screening visit. All participants will sign an informed consent form for all trial procedures and will have the option to enter a sub-study investigating cerebrospinal fluid (CSF) biomarkers, with a recruitment goal of 106 of the 330 participants.

All participants will undergo genetic testing through the PD-Frontline online study (https://pdfrontline.com) or equivalent service prior to enrolment. This involves the collection of a saliva sample from participants, extraction of DNA, sequencing of *GBA1* with Nanopore long read sequencing, Sanger confirmation of positive results [22], and LRRK2 genotyping with the KBiosciences Competitive Allele Specific PCR SNP genotyping system.

### Randomisation and blinding

Participants will be randomised 1:1 to receive either ambroxol or placebo. Randomisation will be implemented using a minimisation algorithm incorporating a random element to achieve overall balance between the randomised groups by research site, Movement Disorders Society–Unified Parkinson’s Disease Rating Scale (MDS-UPDRS) part III, *GBA1* mutation status, age, time since PD diagnosis, and levodopa equivalent dose.

The treatment allocation will be concealed from all trial personnel, including investigators, pharmacy staff, research teams at sites, participants, and the analysing trial statistician prior to assignment and during the trial, until the final participant has completed the double blind phase, and the database is locked.

Before database lock, the only data summarised by treatment allocation will be within reports to the Independent Data Monitoring Committee (IDMC), which will not be distributed outside of this committee. The unblinded statistician will be responsible for preparing these reports and will be the only person outside the IDMC who will have access to these reports. Unblinded statisticians will be excluded from any discussion on the implementation or planning of the trial.

### Intervention

Participants in the active arm will receive oral ambroxol tablets (each tablet containing 420 mg). During the titration period, they will take one tablet a day (420 mg/day) for 5 days (Days 1–5), followed by one tablet twice a day (840 mg/day) for a further 5 days (Days 6–10); thereafter, one tablet three times a day (1260 mg/day) from Day 11. Participants will continue their intake of three tablets per day (1260 mg/day) for the remainder of the blinded treatment phase, which will last a total of 104 weeks. Each stage of the dose escalation can be prolonged for up to a further 5 days if required by the development of adverse symptoms. Those participants unable to reach dose level three will discontinue IMP but will continue to contribute to trial endpoints in an intention-to-treat analysis.

Participants in the placebo arm will receive placebo tablets, which will be identical to the ambroxol tablets in size, appearance, taste, and container, and will follow an identical titration period.

At the end of the 2-year blinded treatment phase, all participants will enter the open-label extension phase, starting ambroxol one tablet a day (420 mg/day) for 5 days, followed by two tablets a day (840 mg/day) for a further 5 days; thereafter, three tablets a day (1260 mg/day) for the remainder of the open-label phase, which will last a total of 26 weeks.

### Assessment of participants and outcomes

At screening, participants will sign an informed consent, and adherence to inclusion and exclusion criteria will be confirmed by performing vital signs, ECG, a blood test, a full neurological exam, Beck’s Depression Inventory Second Edition (BDI-II) [23] and Montreal Cognitive Assessment (MoCA) [24]. If participants meet entry criteria, they will be randomised at baseline visit, within 28 days from screening. At baseline visit, all participants will provide blood samples and will be assessed for all outcomes. Additional visits (2 to 6) will take place at 20, 40, 60, 80 and 104 weeks after randomisation, and the end of treatment visit (7) will take place 130 weeks after randomisation, i.e. at the end of the 26-week open label extension period. The assessment schedule is reported in Fig. 1.

**Fig. 1 Fig1:**
[figure not shown]
AsPRO-PD trial diagram

Participants who opted to participate in the CSF sub-study will provide a CSF sample at visit 1 and at visit 6 (104 weeks).

The primary outcome is the sum score of MDS-UPDRS parts I-III (part III measured in OFF medication state) assessed at 104 weeks after randomisation. OFF medication state is defined as not having taken any PD medication for 8 h in the case of short acting agents or ≥ 24 h in the case of longer acting agents (e.g. once-daily dopamine agonists). Irreversible monoamine oxidase type B inhibitors (MAOBIs) will only be stopped the morning of the assessment and then taken after the OFF examination. It is accepted that the long half-life of MAOBIs make alternative arrangements impractical.

Different personnel will assess primary outcome measures from those documenting adverse event data to minimise risk of rater bias/inadvertent unblinding. Secondary outcomes will be assessed non-hierarchically and include the rate of change of MDS-UPDRS composite scores of parts I–III and of part III from baseline to 104 weeks, and the following outcome measures at 104 weeks: the individual scores of MDS-UPDRS parts I, II, III and IV, MoCA, Trial Making Test parts A and B [25], Hooper Visual Organization Test (VOT) [26], Parkinson’s disease 39 item Quality of Life questionnaire (PDQ-39) [27], Patient Global Impression (PGI) Severity and Change [28], EuroQol Eq-5D 5-Level Health Related Quality of Life Questionnaire [29], Non-Motor Symptoms Scale (NMSS) [30], Parkinson’s Disease Comprehensive Response (PD CORE) [31], Dresden Falls Questionnaire (DREFAQ) [32], Clinical Global Impression (CGI) [28], and change in levodopa equivalent dose. Safety and tolerability measures and time to initiation of rescue medication will also be included in secondary outcomes. Mechanistic outcomes include differences in GCase activity, GCase protein levels and alpha synuclein protein levels in blood and CSF and additionally glucosylceramide, neurofilament light chain (NFL), TAU protein and lipid profile in CSF. Further exploratory outcomes are comparison of change in MDS-UPDRS at 104 weeks from baseline by subgroup *GBA1* mutation status, analysis of *GBA1* positive and negative carrier data against placebo, change in MDS-UPDRS at 130 weeks from baseline, change in the gut microbiome composition at 104 weeks from baseline, and change in UPSIT at 104 weeks from baseline.

### Safety monitoring

At all in-person trial visits, vital signs, ECG, and blood tests will be collected. Full blood count, liver and kidney function tests, and coagulation screening will be evaluated.

Additionally, phone calls to ensure adherence and evaluate safety will be carried out at weeks 1, 2, 10, 30, 50, 70, 90, 105, 106, and 114 post-randomisation.

Adverse events (AE) will be recorded at each visit and the investigator will evaluate seriousness, severity and causality, ultimately deciding whether a participant can continue to take the treatment. All AE will be reported, disregarding their causality. The following adverse reactions are potentially related to ambroxol hydrochloride: nausea, vomiting, rash, abdominal pain, diarrhoea, anaphylactic reaction, urticaria, dyspepsia, dry mouth, numbness in throat and mouth, and changes in sense of taste.

Women of child-bearing potential will carry out a serum pregnancy test at screening, and a urine pregnancy test at each in-person visit. Adequate contraception for the duration of the study is required for such women and their male partners.

### Statistical considerations

The sample size is calculated based on estimating the average difference in MDS-UPDRS at Week 104 conditional on the baseline scores, at the 2.5% significance level in a one-sided test of superiority of ambroxol over placebo. A standard deviation of 14, a correlation of 0.7 between the outcome and baseline and 20% attrition percentage was assumed based on previous studies and data from the Exenatide-PD trial [33]. The proposed sample size has 90% power to detect the minimum important difference of 4 in MDS-UPDRS I–III at the 2.5% (one-sided) significance level.

Summary measures will be presented as means and standard deviations for normally distributed variables, medians and interquartile ranges for non-normally distributed variables, and frequencies and percentages for categorical variables.

A multilevel repeated measures linear regression model will be used to estimate the difference (with 95% confidence intervals) in MDS-UPDRS (parts I–III) scores between ambroxol and placebo, following the intention-to-treat principle. The model will include fixed effects for the intervention groups (ambroxol or placebo) and the minimisation factors (i.e. the co-variates) *GBA1* mutation status (wild-type, severe variant carrier, non-severe variant carrier), age, time since diagnosis and the levodopa equivalent dose. Baseline scores will be accounted for using a random intercept term to address clustering of repeated measurements within participants. Additionally, a random effect for site and patient effect will be included to take account of clustering. This model for the primary outcome will be extended using an interaction term to investigate whether the effect of treatment differs according to *GBA1* status, as a pre-specified subgroup analysis.

Changes to participants’ standard Parkinson medication (e.g. levodopa etc.) will be allowed during the trial. A levodopa equivalent dose (LED) will be calculated, and a causal mediation analysis may be carried out as a sensitivity analysis of the primary outcome to assess if differences in LED levels between treatment arms mediate any observed treatment effect on the primary outcome.

No formal interim analyses are planned; however, the IDMC will review trial and safety data at least annually and advise the study sponsor on the continuation or modification of the trial. Trial decisions will be taken by the Trial Management Group, with guidance and oversight from an independent committee, the Trial Steering Committee. Trial operations are delivered by the UCL Comprehensive Clinical Trials Unit.

All efforts will be made to ensure that the primary outcome data are collected for all participants. We will consider using causal mediation analysis if > 20% of participants discontinue treatment early to assess whether any potential differences in treatment adherence by arm may mediate the effect of treatment on the primary outcome. Prior to database lock, a detailed statistical analysis plan (SAP) will be produced, indicating all planned analysis and endpoints.

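### The primary repeated-measures model, as described, has no visit term or week-104 contrast, so its treatment coefficient is not the week-104 difference that defines the endpoint and the sample size

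*Protocol article*

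**What the plan says.** All references are to the Methods of the protocol article.

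- **Endpoint.** Under Assessment of participants and outcomes, the primary outcome is the sum of MDS-UPDRS parts I to III, "assessed at 104 weeks after randomisation". Rate of change to week 104 is listed separately, as a secondary outcome.
- **Sample size.** Statistical considerations bases it on "estimating the average difference in MDS-UPDRS at Week 104 conditional on the baseline scores".
- **Visits.** "Additional visits (2 to 6) will take place at 20, 40, 60, 80 and 104 weeks after randomisation".
- **Primary model.** "A multilevel repeated measures linear regression model will be used to estimate the difference (with 95% confidence intervals) in MDS-UPDRS" parts I to III. On its terms: "The model will include fixed effects for the intervention groups (ambroxol or placebo) and the minimisation factors (i.e. the co-variates", followed by GBA1 status, age, time since diagnosis and levodopa equivalent dose. Random effects for site and patient are added.
- **Baseline.** "Baseline scores will be accounted for using a random intercept term to address clustering of repeated measurements within participants". The baseline score is not listed as a fixed covariate.
- **Interaction.** The only one named is for the subgroup analysis, in which the model is "extended using an interaction term to investigate whether the effect of treatment differs according to" GBA1 status.

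**The concern.** A treatment main effect fitted to repeated scores, with nothing that lets the effect change from visit to visit, estimates one common difference across those scores. The declared endpoint is the difference at one visit. The two agree only if the effect is the same at every modelled time point.

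The article's own rationale points the other way. The trial aims to slow progression, and the Discussion justifies two years of treatment as the least time in which a meaningful difference could be expected to appear. Early visits should then show little difference, and an averaged coefficient would include them.

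The baseline sentence adds to the problem. A random intercept carries baseline information only if the baseline score is one of the outcome rows. No treatment difference is expected at baseline, so that row pulls a common treatment coefficient toward zero whatever the shape of the later effect.

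At stake is what the primary estimate, confidence interval and p-value refer to, and whether the stated 90% power applies to them.

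**Working it through.** **1. Reproduce the plan's figure.** Inputs from Statistical considerations: SD 14, baseline correlation 0.7, difference 4, one-sided 2.5%, power 90%, attrition 20%.

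- Residual SD = 14 × √(1 − 0.7²) = 10.0
- n per arm = 2 × (1.960 + 1.282)² × 10.0² / 4² = 131.3, rounded up to 132; total 264
- 264 / 0.80 = 330, the stated number
- SE = √(2 × 10.0² / 132) = 1.23; power = Φ(4/1.23 − 1.96) = 90.2%

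The sample size is therefore a baseline-adjusted comparison at week 104 alone, and it is correct for that comparison.

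**2. What the described model targets.** With complete data, a random-intercept model with a treatment main effect only gives the equally weighted mean of the visit-specific differences. The article gives no effect trajectory, so two are assumed.

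- Linear growth to 4 points: differences of 0.77, 1.54, 2.31, 3.08 and 4.00 at weeks 20, 40, 60, 80 and 104.
- Constant effect: 4 points at every follow-up visit.

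| Rows in the model | Linear growth | Constant effect |
|---|---|---|
| Five follow-up visits | 4 × (304/5)/104 = 2.34 | 4.00 |
| Baseline plus five visits | 4 × (304/6)/104 = 1.95 | 4 × 5/6 = 3.33 |
| Baseline plus week 104 only | 4/2 = 2.00 | 4/2 = 2.00 |

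Here 304 = 20 + 40 + 60 + 80 + 104.

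**3. Illustrative power under linear growth.** Assumptions: 132 per arm, SD 14 at every visit, equal correlation ρ = 0.7 between all time points. Power = Φ(target/SE − 1.96), with SE = √(2V/132).

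- Five visits, baseline as covariate: V = 196 × [(1 + 4ρ)/5 − ρ²] = 52.9; SE 0.90; power 74%
- Five visits, no baseline covariate: V = 196 × (1 + 4ρ)/5 = 149.0; SE 1.50; power 34%
- Six rows including baseline: V = 196 × (1 + 5ρ)/6 = 147.0; SE 1.49; power 26%
- Week-104 contrast, baseline-adjusted: SE 1.23; power 90%

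The step from 90% to 74% comes from averaging over visits. The further fall to 34% or 26% comes from how baseline is handled.

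**4. Sensitivity to ρ.** For the five-visit average with a baseline covariate, power is 67%, 74%, 86% and 98% at ρ = 0.6, 0.7, 0.8 and 0.9. The week-104 contrast at the same values has 83%, 90%, 97% and nearly 100%. Under this equal-correlation pattern, only ρ = 0.7 matches the plan's own baseline correlation. Over the same range, power is 38% to 29% without a baseline covariate and 28% to 22% with baseline as an outcome row.

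**5. The favourable case.** With a constant effect, a baseline covariate and ρ = 0.7, averaging loses nothing: Φ(4/0.895 − 1.96) = 99%.

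**The case against.** The strongest reply is that this is an omission in a condensed article. The article says the model will include certain terms, not only those terms, and it promises a detailed statistical analysis plan before database lock. The list does look abbreviated: MDS-UPDRS part III is a minimisation factor under Randomisation and blinding but is absent from the fixed effects. Endpoint and sample size both point to week 104, so the intended quantity is recognisable. The text also does not say which visits enter the model.

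Much of this stands. A reader might infer that visit terms have been ruled out, or that averaging over all five visits is settled policy. The text supports neither. A reader might also infer that the trial has only about 30% power. That figure needs linear growth, assumed correlations and no baseline covariate, and the last of these is a separate matter from the missing visit terms. Nor is it established that dropout would bias the result. Without a visit effect, unequal late dropout could distort the coefficient, but the article gives no sign of unequal dropout and the effect has not been quantified.

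What does not stand is the claim that the model was simply left for later. The article gives the fixed effects, the random effects, the treatment of baseline and a subgroup interaction, yet no term that ties the model to week 104. Uncertainty about the visits does not rescue it: with baseline and week 104 alone as outcome rows, the coefficient targets 2.0 points, not 4.

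**Conclusion.** The point holds as an inconsistency between the stated endpoint and the stated model. Endpoint and sample size refer to the week-104 difference given baseline; the model as described yields an average over the modelled time points. That mismatch depends on no numerical assumption.

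Its size does. With all five follow-up visits, the target lies between 2.34 points (linear growth) and 4 points (constant effect), or between 1.95 and 3.33 if baseline is an outcome row. The power loss attributable to averaging alone, under linear growth and a correlation of 0.7, is from 90% to about 74%; under a constant effect with a baseline covariate there is none. It would be wrong to conclude that a true 4-point benefit must be reported at half its size, because that needs both linear growth and the baseline row. It would also be wrong to conclude that 330 participants is too few: that number is right for the week-104 contrast.

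**What to change.** Revise the model description, and carry the same wording into the statistical analysis plan:

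- add visit as a categorical fixed effect, and treatment by visit;
- adjust for the baseline score, either as a fixed covariate or by keeping baseline as an outcome with the arm means constrained equal;
- say which visits enter the model, and name the treatment contrast at week 104 as the primary estimate;
- apply the GBA1 interaction to that week-104 contrast.

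The cost is wording only. No extra data or participants are needed and N stays at 330. The change should be made before database lock.

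### The trial is sized on a Week 104 comparison conditional on baseline, but the primary model as worded has no baseline MDS-UPDRS covariate, so the stated 90% power depends on a specification the text does not give

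*Protocol article*

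**What the plan says.** All but two of these points are in the protocol article under Statistical considerations.

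- **Target of the sample size:** "estimating the average difference in MDS-UPDRS at Week 104 conditional on the baseline scores", tested "at the 2.5% significance level in a one-sided test of superiority of ambroxol over placebo".
- **Assumptions:** "A standard deviation of 14, a correlation of 0.7 between the outcome and baseline and 20% attrition percentage was assumed".
- **Claim:** the planned number "has 90% power to detect the minimum important difference of 4 in MDS-UPDRS I–III". The total of 330 is given under Participants.
- **Primary model:** a multilevel repeated measures linear regression. Its fixed effects are treatment and what the text calls the minimisation factors, listed as *GBA1* status, age, time since diagnosis and levodopa equivalent dose.
- **Baseline:** "Baseline scores will be accounted for using a random intercept term to address clustering of repeated measurements within participants". The next sentence adds random effects for site and for patient.
- **Minimisation:** Randomisation and blinding names six factors. Four are the fixed effects above and a fifth, site, enters as a random effect. The sixth, "Rating Scale (MDS-UPDRS) part III", does not appear in the model.

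**The concern.** The sample size and the model stand in the same section and do not visibly match. A correlation of 0.7 cuts the outcome variance to 1 − 0.49 = 0.51 of its unadjusted value, but only if the treatment contrast is adjusted for baseline. A participant-level random intercept describes how measurements on one person hang together. It does not by itself remove from the between-arm comparison the variation that baseline explains. The only sentence on baseline therefore names a device that does not do the stated job unless further conditions hold, and those conditions are not stated.

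The missing part III score is a second mismatch. It is part of the primary endpoint and allocation is balanced on it. If neither it nor the baseline total is in the model, the model-based standard error ignores that balance and is too large.

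At stake is whether the primary analysis of a phase 3 trial has the precision it was sized for.

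**Working it through.** **Inputs** (Statistical considerations, Participants, Randomisation and blinding): difference 4; SD 14, so variance 196; r = 0.7; one-sided alpha 0.025 (z = 1.960); power 90% (z = 1.282); attrition 20%; allocation 1:1; N = 330.

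**Step 1: reproduce the plan's figure.** With adjustment for baseline,

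n per arm = 2 × (1.960 + 1.282)² × 196 × 0.51 / 4² = 131.3, rounded up to 132.

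Total 264, and 264 / 0.8 = 330. The match is exact.

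Without the factor 0.51, n per arm is 257.4, rounded up to 258, and 516 / 0.8 = 645 (646 for equal arms). The figure of 330 thus depends on conditioning on baseline.

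**Step 2: power under each reading of the model.** Power = Φ(4 / SE − 1.960), with 132 per arm.

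| Reading | Variance per person | SE | Power |
|---|---|---|---|
| Baseline as fixed covariate | 196 × 0.51 = 99.96 | √(2 × 99.96 / 132) = 1.231 | 90.2% |
| Baseline as an outcome row, equal arm means at baseline, treatment-by-visit terms | 99.96 | 1.231 | 90.2% |
| Difference in change from baseline | 2 × 196 × 0.3 = 117.6 | √(2 × 117.6 / 132) = 1.335 | 85.0% |
| Week 104 contrast, post-baseline rows only | 196 | √(2 × 196 / 132) = 1.723 | 64.1% |

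The second row equals the first for this reason. With equal baseline means, the generalised least squares estimate is the Week 104 difference minus 0.7 times the observed baseline difference. Its variance per person is 196 × (1 + 0.49 − 2 × 0.49) = 196 × 0.51.

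**Step 3: allow for the other covariates in the last row.** If *GBA1* status, age, time since diagnosis and levodopa equivalent dose explain a share R² of the outcome variance (assumed; the article gives no figure), the variance is 196 × (1 − R²). Power is 68.7% at R² = 0.1 and 73.7% at R² = 0.2. It returns to 90.2% only at R² = 0.49.

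**Step 4: why the contrast should be named too.** The article lists a treatment effect but no treatment-by-visit term. Suppose a single treatment effect were fitted across the five post-baseline visits (weeks 20, 40, 60, 80 and 104).

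- SE = √(2 × 196 × (1 + 4 × 0.7) / 5 / 132) = 1.502.
- Power is 75.9% if the effect is 4 at every visit.
- If the effect grows linearly to 4 at Week 104, the average effect is 4 × (304 / 5) / 104 = 2.34 and power is 34.3%.

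Both effect shapes are assumptions. They show only that the repair should fix the contrast as well as the baseline term.

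Steps 2 to 4 assume complete data in 264 participants and a common correlation of 0.7 between visits.

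**The case against.** The strongest reply is that baseline may be meant as one of the repeated measurements. The article says that baseline is accounted for, places this inside a repeated measures model, and declares its intent to compare arms conditional on baseline. With equal arm means at baseline and treatment-by-visit terms, such a model delivers 90.2%, exactly as planned. This stands. A reader might infer that baseline is not adjusted for at all, that the 90% power is lost, or that confidence intervals will be 40% wider (1.723 / 1.231 = 1.40). The document does not support any of these as certain. They hold only if baseline rows are left out and, for the full 40%, if the other covariates explain nothing. Naming a patient effect twice is loose drafting and does not show that baseline is absent.

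Second, minimisation on part III limits baseline imbalance, so 1.723 overstates the true sampling variation. This is right but does little to rescue the power. In the limiting case where allocation balances baseline perfectly, the true SE is 1.231 while the test still uses 1.723. Power is then Φ((4 − 1.960 × 1.723) / 1.231) = Φ(0.51), about 69%, and the one-sided type I error is about 0.3%.

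Third, part III is contained in the I–III total, so leaving it out costs little once that total is conditioned on. This stands, and the omission alone is a minor point.

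Fourth, this is a condensed article and a detailed analysis plan is promised before database lock. Parameterisation can be left to that plan. But the article chose to say how baseline is handled, and what it says does not match the basis of its own sample size.

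**Conclusion.** The point holds as a mismatch between the stated model and the stated power. The sample size is right for an analysis that conditions on baseline. The model as worded does not establish such an analysis, and it omits one of the minimisation factors it claims to include. For a Week 104 comparison with 132 evaluable per arm, power runs from 90.2% (true conditioning) through 85.0% (change from baseline) to 64.1% (post-baseline rows only), or 69–74% in that last case if other covariates explain an assumed 10–20% of variance. The loss is conditional: between none and 90.2 − 64.1 = 26.1 points. These figures rest on the article's SD, correlation and attrition, on complete data in 264 participants, and on a common correlation across visits. It matters because the wording allows materially different primary analyses.

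**What to change.** Replace the sentence on baseline with one of two explicit statements:

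- baseline MDS-UPDRS I–III enters as a fixed covariate, with a baseline-by-visit term; or
- a constrained-baseline longitudinal model is used, with baseline in the outcome vector and a common baseline mean across arms.

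In either case, state that the model has treatment-by-visit terms and that the Week 104 contrast is the primary estimate. List the patient-level random effect once. Add baseline part III to the covariates, or say that the baseline I–III total covers that minimisation factor. Carry the same wording into the analysis plan before database lock.

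The cost is wording only. All outcomes are already assessed at the baseline visit, and N = 330 stays as it is.
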